### Sample size

The sample size estimation was focused on the primary outcome (log transformed RMSSD), assuming that a difference of about 12–15% between the two conditions (EDA vs. no EDA) is scientifically reasonable and clinically relevant [44–46]. The within person standard deviation (SD) of the differences of the log transformed RMSSD between a low-stress and high-stress situation was estimated at 0.64 ms [47]. To be able to determine a difference of 12% and 15% between the two conditions as significant with an alpha level of 0.05 and a power level of 0.80 in a paired sample t-test, the sample size needs to be between 26 and 40 participants, respectively. This corresponds approximately to a medium-sized effect (i.e., Cohen’s d of about 0.45–0.55). To be cautious and compensate for possible missing records, we plan to recruit a total sample of 50 participants.

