**Results:**

A sample size of 26–40 participants was estimated to provide 80% power (α = 0.05) to detect differences of 12–15% between conditions. Ethical approval was obtained from the Swissethics (CER-VD 2024-01573), and participant recruitment is ongoing, with 27 drivers enrolled as of June 2025.

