In this study we aim to assess whether the use of EDA in public transport companies constitutes a new occupational stressor for bus drivers with ultimate harmful effects on their health and well-being. For this work we formulated the following research hypotheses. First, if EDA use acts as an additional stressor, driving with EDA would activate the body’s stress regulation systems, primarily of the autonomous nervous system (ANS) axis, whose effects on heart rate and HRV (usually a decrease in HRV) are immediate and can be measured within 1–5 seconds. If the trial showed that driving with EDA decreases the bus driver’s HRV in comparison to driving without EDA, it would indicate the inability of the ANS to adapt to the EDA presence in the bus drivers’ workplace as an effective stress regulation mechanism. Secondly, we hypothesize that driving with EDA would correspond to a higher psychological stress perceived by bus drivers at the end of the working day, compared to the working days of driving without EDA. Indeed, in addition to the continuous driving performance monitoring and feedback, the EDA of interest generates detailed reports informing bus drivers of their overall performance to ultimately improve their driving behavior. This self-training module may act as additional burden on the bus driver, especially in the case of unsatisfactory performance. Finally, we hypothesized that if EDA acts as a true stressor, it will also activate the Hypothalamic-Pituitary-Adrenal (HPA) axis of stress regulation via neuroendocrine pathway. Indeed, the HPA axis requires a more substantial or sustained stressor to be activated and takes minutes to hours because it involves hormonal signaling cascades. That would result in increased level of biomarkers (i.e., cortisol and cortisone).

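### The printed inputs (12–15% difference, SD 0.64) need 199 and 124 participants, not 26–40, and the order of the two sample sizes is reversed

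*Protocol article*

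**What the plan says.** The calculation is in the Protocol article, Methods, Sample size. It concerns the primary outcome: "The sample size estimation was focused on the primary outcome (log transformed RMSSD"). The target is set by "assuming that a difference of about 12–15% between the two conditions (EDA vs. no EDA) is scientifically reasonable and clinically relevant". The variability input is the within-person SD of the "differences of the log transformed RMSSD between a low-stress and high-stress situation was estimated at 0.64 ms", taken from a cited source. With alpha 0.05, power 0.80 and a paired t-test, the section concludes that "the sample size needs to be between 26 and 40 participants, respectively", with 12% named before 15%. It then adds: "This corresponds approximately to a medium-sized effect (i.e., Cohen’s d of about 0.45–0.55"). Recruitment is set at 50 to allow for missing records.

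The Results paragraph of the Abstract repeats the claim, giving 26–40 participants for 80% power "to detect differences of 12–15% between conditions".

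The direction of interest is a fall. The Background says that the hypothesis would be supported if "driving with EDA decreases the bus driver’s HRV in comparison to driving without EDA".

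**The concern.** Everything needed to redo the calculation is printed in one paragraph, and the result does not follow. An SD of 0.64 on the log scale is large beside a 12–15% change in RMSSD, so a medium-sized d is not plausible from those inputs. The order is also impossible, because a smaller difference cannot need fewer participants at the same SD, alpha and power.

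This is the only power justification for the primary endpoint, and it is repeated in the Abstract. As printed, a reader cannot tell what size of effect the trial can detect. The answer matters for a trial that asks whether EDA is a new stressor, because one reading of the inputs gives the planned 50 ample power for a 12–15% fall and another gives less than even odds of detecting it.

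**Working it through.** **Inputs, all from the Sample size section unless noted.** Difference x = 12% or 15%; SD of paired log differences 0.64; alpha 0.05; power 0.80; paired t-test; planned N = 50. The Background makes the effect a decrease. Sidedness is not stated, so two-sided is assumed and one-sided is shown as a variant. Natural logs are assumed.

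**Formulas.** d = |ln(1 − x)| / SD. Normal approximation: n = ((1.960 + 0.842) / d)² = 7.849 / d². The final n and power come from the noncentral t distribution.

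**Step 1: do the plan's N and d agree?** Approximately.
- d = 0.45: 7.849 / 0.2025 = 38.8, so 39 (noncentral t: 41).
- d = 0.55: 7.849 / 0.3025 = 25.9, so 26 (noncentral t: 28).

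The printed 26–40 therefore fits the printed d. The break lies between d and the inputs before it.

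**Step 2: does d follow from the difference and the SD?** No.

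| Fall in RMSSD | Log difference | d with SD 0.64 | n, normal | n, noncentral t | Power at N = 50 |
|---|---|---|---|---|---|
| 12% | 0.1278 | 0.200 | 197 | 199 | 28% |
| 15% | 0.1625 | 0.254 | 122 | 124 | 42% |

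**Step 3: what could be detected with SD 0.64?** At 80% power:
- 26 participants: d = 0.572, or 0.366 log units, a fall of about 31%.
- 40 participants: d = 0.454, or 0.291 log units, a fall of about 25%.
- 50 participants: d = 0.404, or 0.259 log units, a fall of about 23%.

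**Step 4: other readings of the printed inputs.** Required n (noncentral t), 15% first and then 12%:
- one-sided test: 98 and 157;
- 0.15 and 0.12 taken directly as log units: 145 and 226;
- a rise instead of a fall, ln(1 + x): 167 and 253;
- base-10 logs: 648 and 1045.

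None comes near 26–40.

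**Step 5: unstated inputs that would come close.**
- *A smaller SD.* The SDs implied by the printed d are 0.1278 / 0.45 = 0.284 and 0.1625 / 0.55 = 0.295. An SD of 0.28 gives n = 40 for 12% and 26 for 15%.
- *Averaging over shifts.* Five independent shift pairs per driver give 0.64 / √5 = 0.286. Then d = 0.447 and 0.568, n = 42 (12%) and 27 (15%), and power at 50 is 87% and 98%.
- *Percentage of the mean log value.* With SD 0.64, 0.291 / 0.12 = 2.42 and 0.366 / 0.15 = 2.44. So 12% and 15% of a mean log RMSSD near 2.4 would reproduce 40 and 26. The article gives no such mean, and these differences are falls of about 25% and 31% in RMSSD, not 12% and 15%.

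**Step 6: order.** At any fixed SD, n is proportional to 1/d², so 12% must need the larger sample. The text gives it the smaller one.

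**Step 7: unit.** A difference of logs has no unit, so an SD on that scale cannot be in ms.

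**The case against.** The strongest defence is averaging. The Methods paragraph of the Abstract says that RMSSD is averaged over intervention and control shifts, with at least five intervention shifts. If 0.64 applies to a single pair of situations, five pairs per driver bring the SD to 0.286 and nearly recover both the printed N and the printed d. The source of the 0.64 is not available here, and it describes a low-stress against high-stress contrast rather than EDA against no EDA. The Statistical analyses section also plans a mixed model on repeated measures, so one unaveraged pair per driver may not represent the trial's real precision.

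This is a credible explanation, but it does not remove the error. The Sample size section does not mention averaging and presents 0.64 as the SD that enters the paired t-test. Dividing by √5 also requires that the EDA effect does not vary between drivers. As an illustration only, assume that the SD of the true driver-specific effects is 0.2. The variance of a driver's mean difference is then 0.04 + (0.4096 − 0.04) / 5 = 0.114, the SD is 0.338, and n becomes 57 (12%) and 36 (15%), against 42 and 27 when that SD is zero. Further, the Primary outcome measurement and Experimental phase duration sections guarantee only 5 hours per condition, and no number of control shifts is given.

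A reader might infer that the trial is simply underpowered, with 28–42% power in place of 80%. The article does not support that as a flat statement. It shows that the inputs and the result cannot both be right, but not which one is misprinted. Nor does it say that a non-significant result would be read as absence of stress; it commits to showing 95% confidence intervals.

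**Conclusion.** The sample size statement is wrong as printed. Its own inputs give d = 0.20–0.25 and 199 (12%) or 124 (15%) participants, against a printed d of 0.45–0.55 and N of 26–40. This rests on natural logs, a two-sided test and percentages of RMSSD itself; the alternatives tried also miss by a wide margin. The reversed order is an error whatever the SD.

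The consequence for power is conditional. If 0.64 is the SD of each driver's EDA minus non-EDA difference, 50 participants give about 28% power for a 12% fall, 42% for 15%, and 80% only for about 23%. If five independent shift pairs were averaged and the effect does not vary between drivers, power at 50 is 87–98%. If the percentage was taken of the mean log value, the printed N fits, but the detectable difference is a fall of about 25–31% in RMSSD.

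**What to change.** Keep 50 participants. In the Sample size section, state the SD that entered the calculation, the scale on which 12–15% is measured, and any averaging over shifts. Remove ms from the log-scale SD and give the larger N for 12%. Then restate N, d and power consistently there and in the Results paragraph of the Abstract, according to what was done:

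- If 0.64 stands unaveraged: report power at 50 of about 28% for a 12% fall and 42% for 15%, with about 23% as the fall detectable at 80% power.
- If averaging over shifts was used: print the resulting SD, the number of shift pairs assumed, and the assumptions on independence and on variation of the effect between drivers.
- If the percentage was taken of the mean log value: print that mean and restate the detectable difference as a change in RMSSD.

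The cost is wording only. No participants are added and conduct does not change. In the first and third cases the published claim becomes less favourable.

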### Statistical analyses

Within-person differences of the continuous log-transformed RMSSD for EDA vs. non-EDA driving shifts will be calculated and shown with SDs and 95% confidence intervals. The resting RMSSD average will be calculated based on the HRV measurement during one non-working night.

Mixed effects models with a random effect per participant (accounting for within subject correlations across repeated measures) and a random effect per day nested within the random effect per subject (to account for repeated measures per day within subjects) will compare RMSSD on EDA driving shifts versus on non-EDA driving shifts adjusted for the relevant subject-specific (e.g., age, sex, BMI), physiological (e.g., lung function parameters and biomarker level), exposure-related (e.g., solar UV, heat and cold), and driving shift specific (e.g., heavy traffic, rural vs. urban routes) covariates and potential confounders.

Potential bias that may arise from usage of different bus models. In case of different bus distributions, statistical models will be adjusted for exposures and bus characteristics which differ significantly. This adjustment will be possible by using the Swiss Bus Exposure Matrix [33] that contains exposure data on seven types of physical and chemical hazards and the Bus Ergonomics Matrix [32] that contains six scores of biomechanical and ergonomic constrains for 705 bus models that have been used in the last 40 years in Switzerland. All the statistical analyses will be performed using Stata and/or R software.

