**Methods:**

The EDA tested in this trial is called “NAVIG”. Buses will be assigned randomly. Operating EDA-equipped vehicle will be considered as intervention condition, operating vehicle without EDA as control. Each participant will be monitored for 10 working days maximum to accumulate at least 5 intervention shifts during the trial. Heart rate variability (HRV) will be continuously recorded during working hours to assess autonomous stress responses. The root mean square of successive differences (RMSSD) will be averaged over intervention and control shifts to enable within-subject comparisons between intervention and control conditions. Subjective stress levels will be evaluated using the self-report instruments: Cohen’s perceived stress scale at baseline and visual analogous scale at baseline and daily. Moreover, neuroendocrine stress biomarkers (salivary cortisol and cortisone) will be collected repeatedly across shifts, as additional outcomes. Mixed-effects models with participant’s ID as a random effect variable will be used to compare stress outcomes between EDA and non-EDA driving conditions. Models will be adjusted for potential confounders.

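### The primary mixed model has no EDA effect that varies between drivers, so it can understate the standard error and inflate type I error if drivers respond differently

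*Protocol article*

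**What the plan says.** All references are to the protocol article.

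- **Statistical analyses, first random effect.** The section specifies "Mixed effects models with a random effect per participant (accounting for within subject correlations across repeated measures").
- **Statistical analyses, second random effect.** A day-level term is added in these words: "and a random effect per day nested within the random effect per subject (to account for repeated measures per day within subjects").
- **Statistical analyses, the comparison.** The stated purpose of this model is that it "will compare RMSSD on EDA driving shifts versus on non-EDA driving shifts". Covariates at subject, physiological, exposure and shift level are also to be included.
- **Statistical analyses, the paired summary.** The section opens with a separate plan: "Within-person differences of the continuous log-transformed RMSSD for EDA vs. non-EDA driving shifts will be calculated and shown with SDs and 95% confidence intervals".
- **Abstract, Methods.** Only one random effect is named: "Mixed-effects models with participant’s ID as a random effect variable will be used to compare stress outcomes". On the handling of the outcome over shifts, the abstract says that it "will be averaged over intervention and control shifts to enable within-subject comparisons between intervention and control conditions".
- **Sample size.** The trial is sized on a paired t-test. The input is described as "The within person standard deviation (SD) of the differences of the log transformed RMSSD"; its value is 0.64 and it refers to a contrast of low and high stress. This gives 26 to 40 participants; 50 are to be recruited.

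No place mentions an EDA effect that varies between participants, and none says whether the paired summary or the mixed model decides the primary question.

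**The concern.** EDA is a within-driver factor with repeated records in each condition. The question is about bus drivers in general, so the relevant uncertainty includes how much the EDA effect differs from one driver to the next. A model with participant and day intercepts handles differences in level between drivers and between days, but assumes one common EDA effect. Any real difference in response is moved mostly into the residual and then averaged over all shifts, as if more shifts from the same drivers could remove it.

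The protocol itself makes such differences plausible. Under Participant sampling, information and inclusion, it collects baseline data on possible moderators of the effect. The Background expects the NAVIG report to weigh more on drivers who score poorly. Drivers are also asked whether they agree with their score.

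At stake is the confidence interval and p-value of the primary outcome. They may be too optimistic, on an error term that differs from the one behind the sample size.

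**Working it through.** **Step 1. The plan's own figure.** Paired t-test, α = 0.05 (taken as two-sided), power 0.80, d = 0.45 to 0.55 (Sample size). With n = ((1.96 + 0.84)/d)²:

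- d = 0.55 gives 25.9, so 26 (28 with the t distribution).
- d = 0.45 gives 38.8, so 39 (41 with the t distribution).

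The stated 26 to 40 therefore agrees with the stated d. The error term of this test is the SD of the driver-level differences, which contains both response differences and shift-level noise.

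**Step 2. Set-up.** Take n drivers with k EDA and k control days each and a mean EDA effect of zero. The variance of a driver's mean difference is V = τ² + 2σ²/k. Here τ² is the between-driver variance of the EDA effect and σ² the shift/day noise. V is fixed at 0.64² = 0.4096. The share s = τ²/V is not in the document and is varied: s = 0, 0.10, 0.25, 0.50, 0.75, that is, a slope SD of 0, 0.20, 0.32, 0.45, 0.55. The value k = 5 is an assumption, prompted by the abstract's five intervention shifts in at most ten working days.

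**Step 3. Standard errors.**

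- True variance of the mean EDA effect: V/n.
- The intercept-only model pools the driver-by-EDA variation (n − 1 df) with the within-condition variation (2n(k − 1) df). With f = (n − 1)/(2nk − n − 1), its expected variance is (V/n) × [1 − s(1 − f)].

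For n = 50 and k = 5, f = 49/449 = 0.109. At s = 0.50 the bracket is 1 − 0.50 × 0.891 = 0.555 and its root is 0.745. The true SE is 0.64/√50 = 0.0905; the model's SE is 0.0905 × 0.745 = 0.067. Type I error is then about P(|Z| > 1.96 × 0.745) = P(|Z| > 1.46) = 14.4%.

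**Step 4. All shares, n = 50, k = 5.** Simulated values are from 40,000 replicates of the balanced layout.

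| Share s | Model SE / true SE | Type I, formula | Type I, simulated | Paired or random-slope error term |
|---|---|---|---|---|
| 0 | 1.00 | 5.0% | 5.0% | 4.9% |
| 0.10 | 0.95 | 6.1% | 6.2% | 5.0% |
| 0.25 | 0.88 | 8.4% | 8.7% | 5.2% |
| 0.50 | 0.74 | 14.4% | 14.4% | 5.1% |
| 0.75 | 0.58 | 25.9% | 26.2% | 5.1% |

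With n = 26 the simulated values are nearly the same: 5.0%, 6.3%, 8.5%, 14.6% and 26.0%. More drivers do not help.

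**Step 5. Sensitivity.**

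- *Fewer days* (k = 3, n = 26): 5.1%, 5.9%, 8.2%, 12.8%, 21.6%.
- *Nested day intercept actually fitted* (REML, n = 26, 500 replicates): 5.4%, 6.8%, 7.6% and 16.6% at shares 0, 0.10, 0.25 and 0.50. The day effect does not cure the problem.
- *EDA alternating within the day over 5 days*: 4.6%, 5.8%, 7.6%, 12.9%, 22.4%.
- *One averaged value per driver and condition* (k = 1): f = 1, the bracket is 1, and type I error stays at 5% whatever the share.
- *The value 0.64*: V cancels from the ratio in Step 3, so type I error depends on s, k and n. The 0.64 only sets the scale of the standard errors.

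**The case against.** **Inflation is not certain.** A reader might infer that the model's standard error is too small and its type I error above 5% in any case. The document does not support that. With no variation in response, including the case of no effect in any driver, the model holds 5%; at a 10% share it is about 6%. The larger shares combined with an SD of 0.64 also imply strong individual responses: at 50%, exp(±1.96 × 0.45) puts 95% of drivers between roughly −59% and +142%. This stands and makes the point conditional. Since V cancels, however, a smaller SD with the same share gives the same inflation.

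**The article does not say intercept, and detail may sit in an unseen analysis plan.** True. But the text names each random effect and its purpose, and those purposes are the ones that intercepts serve. It fixes a structure without the relevant term.

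**The abstract averages RMSSD over shifts.** With one mean per driver and condition the model would match the paired t-test and the problem would vanish. But a nested day effect and shift-specific covariates such as traffic and route need several records per driver and condition, so this reading does not fit the model in Statistical analyses.

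**The paired differences with confidence intervals are already planned.** They carry the right error term, and this is a real safeguard. The text presents them as a description, while the mixed model is what makes the comparison. If the two disagree, the article does not say which decides.

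**The SD of 0.64 is not the variation in EDA response.** A reader might infer that the trial was sized on exactly that variation. It was not: the figure refers to low- and high-stress situations and mixes response differences with noise in unknown proportion. What remains is that a paired error term includes response variation, and the intercept-only model largely averages it away.

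**Conclusion.** The point holds in conditional form. As described, the primary model leaves out a participant-level EDA effect. If drivers differ in their response and shift- or day-level records are modelled, its standard error for the mean EDA effect is too small. For 5 + 5 days, type I error runs from 5% (no such differences) to about 26% (three quarters of the variance of the differences), with 9% and 15% at shares of one quarter and one half. The share, the number of days per condition and the balance are assumptions; the document gives no basis for choosing among the shares. The null considered is a zero mean effect across drivers, which matches the stated aim. This is a correctable weakness in the analysis, not a flaw in the design, and an analysis with the right error term is already planned alongside it.

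**What to change.** - **Primary model.** For log RMSSD, fit EDA as a fixed effect, with a random intercept and random EDA slope per participant and a random intercept for day within participant. Use Satterthwaite or Kenward-Roger degrees of freedom.
- **Fallback.** State in advance that, if this model does not converge, the primary test uses participant-level mean log differences with n − 1 degrees of freedom.
- **Which result governs.** Say that this analysis decides the primary question, and bring the abstract into line on the random effects and on the averaging of RMSSD.
- **Secondary outcomes.** Do not copy the structure across. Saliva is collected once per working day, so for cortisol and cortisone a day intercept cannot be separated from the residual; use a participant intercept and EDA slope without it. VAS has one rating on days without NAVIG and two on days with it, so it needs a structure that fits those ratings.

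**Cost.** A line or two of text and no new data. Intervals will be somewhat wider when responses vary, and the paired fallback gives up adjustment for shift-level covariates such as traffic and route.

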## Results

The trial started in February 2025. The experimental phase is ongoing and will continue until December 2025. In June 2025, 27 bus drivers were included. Most accepted providing saliva samples and performing optional tests.

